### Outcomes {12}

#### Primary outcome

The primary outcome for this study is the absolute value of the behavioural and emotional wellbeing of the child 12 months post-baseline, as provided by their score on the carer-report Strengths and Difficulties Questionnaire (SDQ) [33].

#### Secondary outcomes

Secondary outcomes are the absolute values for the SDQ at 4 months, and the following outcome measures recorded at 4 and 12 months post-baseline: foster carer’s level of stress as measured by the Parenting Stress Index (short form) (PSI 4-SF) [34]; foster carer’s quality of life and foster carer’s compassion fatigue and burnout (Professional Quality of Life Questionnaire, PRoQOL) [35]; the Child’s capacity for emotional regulation, as measured by the Emotional Regulation Checklist (ERC) [36]; foster carer’s reflective capacity, as measured by the Parental Reflective Functioning Questionnaire (PRFQ) [37]; achievement of personalised goals set by the foster carer (measured by the Carer Defined Problem Scale (CDPS)) [38]. In addition, we will examine placement stability, which is recorded in relation to changes of social worker, change of school, or placement change, and reasons for any change. The data will be recorded using the Placement Stability Log.

See section ‘Plans for assessment and collection of outcomes {18a}’ for a more detailed description of the study outcome measures.

#### Economic evaluation measures:

Economic measures include a version of the Child and Adolescent Service Use Schedule (CA-SUS) designed and tested for use with Children in Care in an earlier feasibility study [31, 39] and the Child Health Utility 9 Dimensions (CHU9D) measure of health-related quality of life [40], proxy reported by foster carers.

### Participant timeline {13}

A CONSORT diagram can be seen below (Fig. 1).

**Fig. 1 Fig1:**
[figure not shown]
CONSORT diagram

After providing consent, participants will be asked to complete the foster carer demographic form and study outcome measures before they are randomly allocated to either the Reflective Fostering Programme (intervention) or the control group. Those participants unable to complete the study measures online will be able to complete them with a member of the research team by telephone. If they cannot be completed either online or by telephone, participants will be provided with paper copies to complete and return (if COVID-19 restrictions allow).

Participants allocated to the intervention arm will begin to attend the Reflective Fostering Programme and those in the control arm will continue with their usual social care support. The intervention period will last between 12 and 14 weeks.

Participants will be asked to complete the same study outcome measures as at baseline at two time-points: 4 months (± 4 weeks) and 12 months (± 4 weeks) after baseline. They will be contacted by the research team by text, email, or phone call and asked to complete the assessments. Those participants unable to complete the study measures online will complete these with a member of the research team by telephone. If they cannot be completed either online or by telephone, participants will be provided with paper copies to complete and return (if COVID-19 restrictions allow).

If the child is no longer with the same carer at either the 4-month or 12-month follow-up, relevant follow-up assessments will still be completed with the original foster carer. Where possible, the child’s current carer will be contacted by the local authority to seek their consent to be contacted by the research team. If they agree to be contacted, a member of the research team will seek consent for the new carer to complete the child-focused measures in relation to the original ‘nominated’ child. The feasibility of doing this has already been established in the Herts and Minds study [48]. The Site Lead, or their delegate, will be responsible for identifying the current carer and approaching them to provide consent to complete study outcome measures.

See Table 1. below for the study schedule.

**Table 1 Tab1:** Study schedule

	Study period						
	Screening	Randomisation	Post-randomisation				Process evaluation
Timepoint	Pre-T0	Pre-T0	T0 Baseline	T0–T1	T1 + 4 months	T2 + 12 months	
**Enrolment:**							
**Eligibility screen**	X						
**Coffee Morning**	X						
**Informed consent**	X						
**Randomisation**		X					
***Fostering Team profile questionnaire***	X						X
**Delivery of Reflective Fostering Programme**				X			
**Attendance Log**				X			
**Facilitator Adherence Rating**				X			
**Incidents of concern Log**				X			
**Assessments:**							
***Demographic information***			X				
***Strengths and difficulties questionnaire***			X		X	X	
***Parenting Stress Index – short form***			X		X	X	
***Professional QoL questionnaire***			X		X	X	
***Emotion Regulation Checklist***			X		X	X	
***Carer Defined Problem Scale***			X		X	X	
***Child Health Utility-9D***			X		X	X	
***Child and Adolescent Service Use Schedule***			X		X	X	
***Placement Stability***			X		X	X	
***Focus Groups with facilitators***							X
***Interviews with foster carers***						X	

### Sample size {14}

Previous experience with this population [39] suggests an effect size ranging from *d* = 0.3 to *d* = 0.4 (i.e. a mean difference in outcome between groups of 0.3 to 0.4 standard deviations) to be clinically relevant. In the first feasibility and evaluation study [28], the baseline standard deviation for the primary outcome measure (SDQ) was 6.8 and showed a change equivalent to an effect size of *d* = 0.3. The current trial compares usual support plus the Reflective Fostering Programme to usual support alone, with the primary outcome assessed at 12 months. We have, therefore, based our sample size on a difference of 0.3 standard deviations in the SDQ, i.e. around 2.0 units.

On the basis of a review of previous clinical trials involving parenting programmes for foster carers, a reasonable estimate for dropout rates for the study is in the range is of 10–15% at the end of intervention (4 months), and 20–25% at 12 months.

The trial is randomised at the individual participant level. However, the nature of the intervention in group format will imply a form of ‘clustering’, i.e. outcomes amongst those in the same intervention groups may be correlated; the strength of this correlation is quantified through an intra-class correlation co-efficient (ICC). Whilst the intervention for the control group has a less clear ‘clustered’ structure, as usual care will vary according to each site’s usual practice, the assumption of zero clustering is likely to be incorrect, due to the delivery by allocated social workers. Therefore, we will consider both arms to have the same degree of ‘clustering’ to avoid potentially under-estimating the sample.

Table 2 provides the estimated statistical power from four different sample sizes across eight different scenarios (varying by assumed ICC and drop-out rate). These estimates assume an average of seven foster carers in each intervention group, an effect size of 0.3 and a fixed statistical significance of 5% (two-sided). A target sample size of 720, 360 per arm, has been fixed for this trial. This was based upon the likelihood of a statistical power between 80 and 90% in most reasonable scenarios.

**Table 2 Tab2:** Statistical power estimates for differing drop-out rates and ICCs

	Drop-out	15%		20%		25%		30%	
	Assumed ICC	0.05	0.10	0.05	0.10	0.05	0.10	0.05	0.10
	770	93%	88%	91%	86%	90%	85%	88%	82%
Total	720	91%	86%	90%	85%	88%	83%	83%	77%
Randomised									
	620	88%	83%	86%	81%	84%	79%	87%	76%
	500	82%	77%	79%	75%	78%	73%	82%	71%

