## Data collection and management

### Plans for assessment and collection of outcomes {18a}

#### Data collection process

All instruments consist of online-administered self-report questionnaires which can be accessed remotely on the foster carers’ own devices (computer, phone, or tablet). A researcher that is blind to study arm will be available to assist with completion of self-report measures by telephone, if required. In this case, participants will be asked not to disclose their group allocation to the researcher. In exceptional cases, and subject to ethical approval in light of COVID-19 restrictions, participants who would rather complete the measures offline, in private and at their own pace will be able to complete paper versions of measures to be returned to a member of the research team who will enter it onto the database (if COVID-19 restrictions allow).

Data will be collected at baseline (immediately prior to the intervention), 4 months post-baseline, and 12 months post-baseline. It is anticipated that a significant proportion (around 70%) of identified children will be with the same foster carer at both the 4- and 12-month follow-up points [42]. Although it is possible that placements may have changed since the initial programme, we have confidence that follow-up data can be collected in the majority of cases even if the nominated child has moved to a new placement. Previous experience has established that it is possible to successfully seek consent from new foster carers to provide follow-up data [45].

Participants will be asked to complete the foster carer demographic form and study baseline measures before randomisation takes place.

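### Table 2 prints impossible power figures at 30% drop-out and ICC 0.05, and understates power at 30% drop-out for the chosen 720; the sample size itself stands

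*Protocol article*

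**What the plan says.** Sample size {14} sets one group of assumptions for the whole of Table 2:

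- **Effect and alpha:** "an effect size of 0.3 and a fixed statistical significance of 5% (two-sided"). The effect is described as "based our sample size on a difference of 0.3 standard deviations in the SDQ, i.e. around 2.0 units", and "the baseline standard deviation for the primary outcome measure (SDQ) was 6.8".
- **Group size:** "These estimates assume an average of seven foster carers in each intervention group".
- **Clustering:** "we will consider both arms to have the same degree of" clustering, so the design effect applies to intervention and control alike.
- **What varies:** "Table 2 provides the estimated statistical power from four different sample sizes across eight different scenarios (varying by assumed ICC and drop-out rate").

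The target of 720 (360 per arm) is then justified: "This was based upon the likelihood of a statistical power between 80 and 90% in most reasonable scenarios". The same section expects drop-out of 20–25% at 12 months.

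Table 2 as printed (power in %, ICC 0.05/0.10):

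| Total N | 15% | 20% | 25% | 30% |
|---|---|---|---|---|
| 770 | 93/88 | 91/86 | 90/85 | 88/82 |
| 720 | 91/86 | 90/85 | 88/83 | 83/77 |
| 620 | 88/83 | 86/81 | 84/79 | 87/76 |
| 500 | 82/77 | 79/75 | 78/73 | 82/71 |

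**The concern.** With effect, alpha, ICC and group size held constant, power must fall as the number randomised falls and as drop-out rises. The ICC 0.05 entries at 30% drop-out break both rules. Down the column they run 88, 83, 87, 82. Along the rows, 620 goes from 84 to 87 and 500 from 78 to 82 between 25% and 30% drop-out. The ICC 0.10 entries in that column (82, 77, 76, 71) are correctly ordered, so the visible contradiction is confined to half the column.

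Table 2 is the evidence shown for the sample size of a definitive trial, and a reader should be able to rely on it. As printed, 720 drops to 77% in one scenario, while 500 appears to hold 82% at the highest drop-out considered.

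**Working it through.** **Inputs, all from Sample size {14}:** d = 0.3; two-sided alpha 5%; m = 7 carers per group; ICC 0.05 or 0.10 in both arms; total N = 770, 720, 620 or 500, allocated 1:1; drop-out q = 15, 20, 25 or 30%.

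**Formula.** Analysed per arm: n = N(1 − q)/2. Group size after drop-out: m' = m(1 − q). Design effect: DE = 1 + (m' − 1) × ICC. Then z = 0.3 × √(n / (2 × DE)) and power = Φ(z − 1.96).

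**Step 1: reproduce the 720 row where it behaves.** At 15% drop-out, n = 306 and m' = 5.95.

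- ICC 0.05: DE = 1.248, z = 3.32, power 91.3% (printed 91).
- ICC 0.10: DE = 1.495, z = 3.04, power 85.9% (printed 86).

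At 20% the formula gives 90.1/84.6 (printed 90/85), and at 25% 88.6/83.1 (printed 88/83). All six entries agree within 0.6 points.

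**Step 2: the 720 row at 30%.** Here n = 252 and m' = 4.9.

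- ICC 0.05: DE = 1.195, z = 3.08, power 86.9% (printed 83).
- ICC 0.10: DE = 1.39, z = 2.86, power 81.5% (printed 77).

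The printed figures are 3.9 and 4.5 points too low.

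**Step 3: the whole table with seven per group.** Each cell shows the computed power, with printed minus computed in brackets.

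| N | ICC | 15% | 20% | 25% | 30% |
|---|---|---|---|---|---|
| 770 | 0.05 | 93.0 (0.0) | 91.9 (−0.9) | 90.6 (−0.6) | 89.0 (−1.0) |
| 770 | 0.10 | 88.1 (−0.1) | 86.9 (−0.9) | 85.5 (−0.5) | 84.0 (−2.0) |
| 720 | 0.05 | 91.3 (−0.3) | 90.1 (−0.1) | 88.6 (−0.6) | 86.9 (−3.9) |
| 720 | 0.10 | 85.9 (+0.1) | 84.6 (+0.4) | 83.1 (−0.1) | 81.5 (−4.5) |
| 620 | 0.05 | 86.9 (+1.1) | 85.4 (+0.6) | 83.6 (+0.4) | 81.6 (+5.4) |
| 620 | 0.10 | 80.4 (+2.6) | 79.0 (+2.0) | 77.3 (+1.7) | 75.5 (+0.5) |
| 500 | 0.05 | 79.1 (+2.9) | 77.2 (+1.8) | 75.1 (+2.9) | 72.8 (+9.2) |
| 500 | 0.10 | 71.5 (+5.5) | 69.9 (+5.1) | 68.2 (+4.8) | 66.3 (+4.7) |

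With seven per group, the 500 row is too high in every cell, by 1.8 to 9.2 points. The 620 row is too high by up to 5.4.

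**Step 4: what the lower rows do match.** Take m = 7.5, 7, 6 and 5 for N = 770, 720, 620 and 500. This corresponds to roughly 51 groups per arm in every row (for 720, 360/7 = 51.4). Now 28 of the 32 cells agree within 2 points. The 500 row becomes 81.8/76.6, 79.9/74.9, 77.7/73.0 and 75.4/70.9, so seven of its eight cells match within 1 point. The four failures all lie at 30% drop-out:

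| Cell | Printed | Computed |
|---|---|---|
| 720, ICC 0.05 | 83 | 86.9 |
| 720, ICC 0.10 | 77 | 81.5 |
| 620, ICC 0.05 | 87 | 82.7 |
| 500, ICC 0.05 | 82 | 75.4 |

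The printed 83/77 for 720 is close to the values computed for 620 (82.7/77.6), and the printed 87 for 620 equals the rounded value for 720. Misplaced entries are a plausible cause, but that is inference.

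**Step 5: an alternative formula.** If the group size stays at seven after drop-out, 720 at 30% gives 84.0/75.9, near the printed pair. But the ICC 0.10 cells for 720 at 15, 20 and 25% become 83.5, 81.2 and 78.7 against 86, 85 and 83 printed, misses of 2.5 to 4.3 points. This does not rescue the table, and no formula can rescue the ordering.

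**The case against.** The best defence is that most of the table is sound. With a group size that varies by row, 28 of 32 cells are right, so the 620 and 500 rows look consistently calculated. Their fault is disagreement with the stated seven, not faulty arithmetic throughout. That stands, and it is why the fix offers two routes. It does not excuse the mismatch: the text gives one average for all rows, and five per group is below the 6–10 carers given in the intervention description.

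Three stronger readings are tempting, and the document supports none of them.

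- **That 720 is underpowered.** The error at 720 runs the other way. Corrected power is above 80% in all eight scenarios, and the 720 figures at the expected 20–25% drop-out are right as printed.
- **That 30% missing data is likely.** The section on data collection says "It is anticipated that a significant proportion (around 70%) of identified children will be with the same foster carer", but that describes placement continuity, not retention. The article plans to approach new carers and is confident of obtaining data in most such cases. Suppose 20–25% loss among children who stay and a share f of new carers consenting. Missing data are then 0.7 × (0.20 to 0.25) + 0.3 × (1 − f): 29–32.5% if f = 0.5, but 20–23.5% if f = 0.8. The article gives no f, and does not say that its 20–25% excludes losses from moves.
- **That the table will be used to accept 620 or 500.** No such fallback appears. Study setting {9} and Recruitment {15} respond to slow recruitment by adding sites.

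**Conclusion.** The concern holds in limited form. The ICC 0.05 entries at 30% drop-out contradict each other whatever formula was used. On the formula that reproduces the rest of the 720 row, power for 720 at 30% is understated by about 4 to 4.5 points. The 500 row, and to a lesser degree the 620 row, do not follow from seven carers per group.

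The replacement values assume a normal approximation, equal clustering in both arms and a group size reduced in proportion to drop-out. The last of these is inferred from the fit, because the article does not state it.

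No design decision changes: 720 remains adequate on the plan's own assumptions, and the 80–90% sentence remains true. Severity is minor to moderate, because the published justification contains wrong figures, including two for the chosen size.

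**What to change.** Choose one of two routes.

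1. **Recompute all 32 cells** with one stated formula and the stated group size of seven, saying that it is reduced by drop-out. At 30% the entries (ICC 0.05/0.10) become about 89/84 for 770, 87/81.5 for 720, 82/75.5 for 620 and 73/66 for 500. The other entries are in the Step 3 table.
2. **If group size was meant to vary by row**, state it for each row and correct four cells at 30% drop-out: 720 to about 87/81.5, 620 at ICC 0.05 to about 83, and 500 at ICC 0.05 to about 75. The 620 entry at ICC 0.10 (76 printed, 77.6 computed) is within tolerance but worth checking against the source calculation.

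Keep 720 and leave the 80–90% sentence as it is. The cost is a correction to one table and a line of text, with no change to sample size, conduct or analysis.

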### Recruitment {15}

Recruitment of foster carers will take place across five cycles of recruitment and delivery (including the pilot phase), timed in such a way that the start of each new wave of Reflective Fostering Programme groups will begin close to the start of a school term (i.e. January, April, and September).

The research team will recruit additional local authorities if recruitment during the first two waves is slower than anticipated (e.g. due to COVID-19 restrictions). This will ensure sufficient numbers of foster carers are recruited to the study. The study team will work with partners including Research in Practice, the Social Care Learning Network, and the Clinical Research Network (CRN) to identify suitable sites. Selection of sites will take into account the geographic and cultural diversity of carers and children in care in the UK, including both more rural and metropolitan settings, in order to ensure that both the intervention and the research study meet the needs of a culturally diverse population living in different parts of the country, and that any obstacles or barriers are identified as part of the process evaluation.

Foster carers will be recruited from local authority sites. Information about the study will be disseminated to foster carers primarily through local authority fostering support teams, but also through local foster carer support groups and by supervising social care workers. All foster carers will be sent information about the study via their local fostering support teams. Foster carers will be encouraged to consult with their supervising social worker about their suitability for the study. If interested, foster carers will be asked to contact the Site Coordinator by phone or email to register their interest in finding out more about the study.

Only one foster carer from each household can join the study as a participant. However, it is recognised that some foster carers randomised to the intervention arm may want to attend the Reflective Fostering Programme together. For those participants, there will be the option for a second carer from the same household to attend together, if they wish to do so. The attendance of both will be recorded, but only the primary carer will be asked to complete study outcome measures. We will report on how many couples choose to attend.

Foster carer recruitment targets for each site will be proportionate to overall size, with the aim to recruit more than 50% of all eligible carers over a 20-month recruitment period in order to meet recruitment targets. This is in line with previous clinical trials involving training programmes for foster carers, where 58–62% of eligible carers are reported to have participated [41]. However, should recruitment be lower than anticipated, potential barriers to dissemination and recruitment will be examined, and if needed, additional local authorities may be recruited.

## Assignment of interventions: allocation

### Sequence generation {16a}

Randomisation will be allocated in a 1:1 ratio, stratified by age of child (4–9 vs 10–13), number of previous placements (1 or less, vs 2 or more) and recruiting region. Consenting foster carers will be randomly allocated to the intervention arm (Reflective Fostering Programme in addition to Usual support) or the control arm (Usual support). The randomisation sequence will be computer generated, blocked in random block lengths of two or four.

### Concealment mechanism {16b}

The allocation sequence will be implemented using randomisation via the REDcap database. Only the database administrator will be permitted to view the allocation sequence and therefore the sequence will be concealed prior to intervention allocation.

Participants will be informed of group allocation by the local Site Coordinator, who will also contact the relevant social worker/s, so that they are aware that the foster carer is taking part in the study. If they are in the intervention group, the Reflective Fostering Programme facilitators at each site will be informed.

### Implementation {16c}

Participants will be randomised as soon as they complete baseline measures. The allocation sequence will be generated by Norwich Clinical Trials Unit (NCTU) Data Management. Randomisation will be managed online (using a tool built by NCTU Data Management) and overseen by the TM.

## Assignment of interventions: blinding

### Who will be blinded {17a}

Both outcome assessors and the trial statistician will be blinded after assignment to interventions. The participants may require the help of members of the research team to help them complete study measures. If so, participants will be reminded not to reveal which arm they are in.

Due to the nature of the intervention, it is not possible for facilitators or foster carers to be blind to allocation. The Site Coordinator will be unblinded so that they can coordinate and plan the Programme delivery. Access to the database will be defined for each role in the study to maintain blinding. The Trial Manager (TM) will also be unblinded to enable any queries from participants relating to the research to be addressed. Within the REDCap study database, the blinded or unblinded status of users will be preserved by database permissions and defensive programming.

### Procedure for unblinding if needed {17b}

The Trial Steering Committee (TSC) is responsible for reviewing safety events and may request that unblinded data from the database be made available to an independent group, should there be concerns raised by the TSC with respect to the number of events and whether this is associated with the intervention.

## Data collection and management

### Plans for assessment and collection of outcomes {18a}

#### Data collection process

All instruments consist of online-administered self-report questionnaires which can be accessed remotely on the foster carers’ own devices (computer, phone, or tablet). A researcher that is blind to study arm will be available to assist with completion of self-report measures by telephone, if required. In this case, participants will be asked not to disclose their group allocation to the researcher. In exceptional cases, and subject to ethical approval in light of COVID-19 restrictions, participants who would rather complete the measures offline, in private and at their own pace will be able to complete paper versions of measures to be returned to a member of the research team who will enter it onto the database (if COVID-19 restrictions allow).

Data will be collected at baseline (immediately prior to the intervention), 4 months post-baseline, and 12 months post-baseline. It is anticipated that a significant proportion (around 70%) of identified children will be with the same foster carer at both the 4- and 12-month follow-up points [42]. Although it is possible that placements may have changed since the initial programme, we have confidence that follow-up data can be collected in the majority of cases even if the nominated child has moved to a new placement. Previous experience has established that it is possible to successfully seek consent from new foster carers to provide follow-up data [45].

Participants will be asked to complete the foster carer demographic form and study baseline measures before randomisation takes place.

